### *Cohort definition*

The original study was intended to be used at any point in the patient pathway; therefore primary validation will be performed and reported based on a sample of patients who were diagnosed in either inpatient or outpatient care settings in Finland.

### *Predictors*

The current study will examine all 17 predictors included in the OxMIS tool. A list of the variables that will be employed in this analysis is presented below (see appendix A). Given the geographical proximity and similar healthcare service provision, including the ways in which health care and administrative data are organized, between Sweden and Finland, we expect the predictor definitions to be broadly similar across both countries. One potential difference is the definition of previous violent crime convictions. The original study used a somewhat broader measure of violent crime offences than what is currently available in the Finnish database that we have access to. More detailed conviction data has been applied for and is expected to be delivered before 31 December 2022. The updated data will include specific penal codes, which could be used to derive an analogous measure of violent crime as in the original study. The narrower measure of violent crime that is currently available in Finland has nevertheless been used in a wide range of criminological studies to date.

### *Missing data*

We have full coverage of all 17 predictors in the Finnish nationwide registry datasets. This includes the two predictors measuring recent psychotropic dispensed medications (i.e., antipsychotics and antidepressants), which had to be partly imputed in the original study due to the fact that the Swedish Prescription Drug Register started on 1 July 2005 whilst the study started on 1 January 2001. The Finnish Prescription Drug Register, however, started on 1 January 1995, thus covering the entire follow-up period of the current study.

### *Censoring*

Similar to the original study, we intend to ignore right-censoring (e.g., emigration and non-suicide deaths) during the follow-up period as it is relatively short and the number of censored individuals are likely quite small. It also reduces complexity of models.

### *Predicted probabilities*

Results will be primarily presented based on risk probabilities, but predictive performance will also be assessed using contingency tables and summary statistics.

### *Presentation of results*

Findings will be presented using both calibration and discrimination, graphically and using tables and summary statistics as appropriate. These will include calibration plots; sensitivity and specificity; AUC.

The report will include descriptive information about the cohort and how it was defined, including any differences from the original cohort in definitions of variables. As far as possible we will follow published guidance on reporting validation study results.

## 5.2 The number of participants

Preliminary data suggest a total sample size exceeding 137,000 individuals, nearly twice that of the original study (n=75,158). A simulation study recommended ballpark minimum figures of 100 events for validating a clinical prediction rule derived using a logistic regression model. If we were to identify an equivalent baseline one-year suicide risk rate as in the original study (0.8%), we would thus have nearly 11 times as many outcome events (i.e. suicides) as the minimum recommendation for validation studies (1096 vs. 100).

## **6. Data management**

### 6.1 Access to data

Direct access will be granted to authorised representatives from the University of Oxford and the host institution, University of Helsinki, for monitoring and/or audit of the study to ensure compliance with regulations.

### 6.2 Data handling and record keeping

The raw pseudonymized data (i.e., using encrypted personal identification numbers) is currently available on the servers of Statistics Finland, which one representative of the University of Oxford

has access to via the high-security remote desktop service of the agency. To gain entry to the remote desktop server (“FIONA”), a user needs to first log in to an accredited Finnish university or governmental agency using a Virtual Private Network (VPN) connection. Once this has been accomplished, the user can then connect to FIONA via a two-step authentication process (e.g., inputting a username and password in addition to accepting the connection on a mobile phone with a number that has been pre-registered by Statistics Finland). It is not possible for FIONA users to transfer any files, either to or from the system. Output files may be exported to the e-mail address of the user by staff members of Statistics Finland following an inspection to determine that they do not include any sensitive individual-level data.

A university researcher at the University of Oxford will initially merge and clean the raw data according to tidy data principles, and subsequently fit the models and generate the proposed post-estimation statistics for model fit. The entire process will be documented using Stata do-files and the RMarkdown reporting tool to facilitate future replication efforts. All data files and codes necessary to replicate the analyses will be stored on the FIONA platform.

## **7. Quality control and quality assurance procedures**

The study will be conducted in accordance with the current approved protocol, relevant regulations, and standard operating procedures.

## **8. Ethical and regulatory considerations**

### **8.1 Declaration of Helsinki**

The Investigators will ensure that this study is conducted in accordance with the principles of the Declaration of Helsinki.

NB. The 2008 Declaration of Helsinki provides detail on what must be included in a protocol: funding, sponsorship, affiliations and potential conflicts of interest, incentives to participate and compensation for harm.

## 8.2. Approvals

This project has been approved by the Ethics Board of Statistics Finland (TK-53-1490-18) and the Finnish Institute for Health and Welfare (THL/2180/14.02.00/2020).

The Investigator will submit and, where necessary, obtain approval from the above parties for all substantial amendments to the original approved documents.

## 8.3. Participant confidentiality

The data provided to the Oxford researcher by Statistics Finland will be fully pseudonymized. The participants are identified by an encrypted participant ID on the electronic database. All documents will be stored securely and only accessible by study staff and authorised personnel. The study fully complies with Finnish privacy laws.

# 11. Finance

## 11.1. Funding

No specific financial arrangements have been made for this study. The project sits within Oxford Health's BRC strategy.

# 12. Publication policy

The Investigators will be involved in reviewing drafts of the manuscripts, abstracts, press releases and any other publications arising from the study. Authorship will be determined in accordance with the ICMJE guidelines and other contributors will be acknowledged.

## Appendix A

### Definition of variables

The table refers to the variables as defined in the original Swedish cohort.

| #  | Variable                         | Type        | Notes                                                                                                                                                                                                                              |
|----|----------------------------------|-------------|------------------------------------------------------------------------------------------------------------------------------------------------------------------------------------------------------------------------------------|
| 1  | Sex                              | Binary      | Male/female                                                                                                                                                                                                                        |
| 2  | Age                              | Continuous  | Age at assessment (allowed range: 15-65). The measure is divided by a constant (10 years) to aid with the interpretation of the regression model.                                                                                  |
| 3  | Previous violent crime           | Binary      | Previous conviction for a violent offence, defined as homicide, assault, robbery, arson, any sexual offense (rape, sexual coercion, child molestation, indecent exposure, or sexual harassment), illegal threats, or intimidation. |
| 4  | Previous drug use                | Binary      | Previous diagnosis of drug use disorder.                                                                                                                                                                                           |
| 5  | Previous alcohol use             | Binary      | Previous diagnosis of alcohol use disorder.                                                                                                                                                                                        |
| 6  | Previous self-harm               | Binary      | Previous diagnosis of alcohol use disorder.                                                                                                                                                                                        |
| 7  | Highest education level          | Categorical | Formal schooling: secondary (to age 16), upper secondary (to age 18), post-secondary (past 18) at the time of assessment.                                                                                                          |
| 8  | Parental drug or alcohol use     | Binary      | Parental diagnosis of drug or alcohol use disorder.                                                                                                                                                                                |
| 9  | Parental suicide                 | Binary      | Parental death by suicide.                                                                                                                                                                                                         |
| 10 | Recent treatment - antipsychotic | Binary      | Prescribed antipsychotics (ATC                                                                                                                                                                                                     |

|    |                                      |        |                                                                                                                                                                                                                                                                                                                         |
|----|--------------------------------------|--------|-------------------------------------------------------------------------------------------------------------------------------------------------------------------------------------------------------------------------------------------------------------------------------------------------------------------------|
|    |                                      |        | code N05A [except N05AN01]) at least once up to 6 months prior to the assessment.                                                                                                                                                                                                                                       |
| 11 | Recent treatment - antidepressant    | Binary | Prescribed antidepressants (ATC code N06A) at least once up to 6 months prior to the assessment.                                                                                                                                                                                                                        |
| 12 | Inpatient at the time of assessment  | Binary | Discharged from an inpatient care setting.                                                                                                                                                                                                                                                                              |
| 13 | Length of first inpatient stay > 7   | Binary | Hospitalized for at least one week during their first inpatient stay.                                                                                                                                                                                                                                                   |
| 14 | Number of previous episodes > 7      | Binary | Previous patient episodes for schizophrenia-spectrum or bipolar disorders. Excluding current episode. A patient episode is defined as one outpatient specialist review (in a mental health service) or one hospitalization (including an overnight stay); two hospitalizations would be considered two periods of care. |
| 15 | Benefit receipt                      | Binary | Receipt of disability pension and/or social assistance benefits prior to the assessment.                                                                                                                                                                                                                                |
| 16 | Parental psychiatric hospitalization | Binary | Parental hospitalization for a psychiatric disorder.                                                                                                                                                                                                                                                                    |
| 17 | Comorbid depression                  | Binary | Comorbid depression diagnosis, only in those with schizophrenia-spectrum disorders.                                                                                                                                                                                                                                     |

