### *Strategy for analysis*

We will employ an incremental strategy to assess the prognostic performance of OxMIS in the Finnish cohort. First, the individual-level prognostic performance will be evaluated in a simple validation perspective, without any adjustment of the model coefficients for the Finnish population. If the model performs poorly in this new population, it will be updated according to a series of pre-specified steps detailed below.

The following steps will be undertaken, proceeding in each case to the subsequent stage only if diagnostic performance is insufficient. The assessment of prognostic performance between steps (i) to (iv) below will be based on statistical significance (retaining the simplest version model for which the subsequent step provides no statistically significant improvement) and the final assessment of performance based on clinical utility – with a particular focus on the equivalent measures reported in the model development paper.

- i. Simple validation: assess the prognostic performance of the existing OxMIS model directly using the Finnish data by applying the existing model directly, without adjusting model coefficients and without adjusting the estimate of baseline risk.
- ii. Updating the baseline risk (analogous to the intercept), holding coefficients of predictor variables at their values from the current model. This may also be seen as adjusting for any systematic risk difference that may be attributable to missing covariates (see subsection below).
- iii. Updating the baseline risk and performing a simple re-calibration of the coefficients of the predictors. This allows for the inclusion of a single re-calibration parameter, i.e. the effect of predictors on the outcome would be assumed to be the same as in the original study, apart from rescaling.
- iv. Additionally re-estimating a subset of the model coefficients. This will be performed only as a last resort as it is likely to lead to a substantively different prediction tool and would allow the associations of the risk markers with the outcome to differ from those found in the original study. If possible, re-estimation will be restricted to a subset of parameters whose coefficients appear to be poorly calibrated.

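### Appendix A gives "Previous self-harm" the definition of alcohol use disorder; coded as written, OxMIS would be scored without any self-harm measure

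*Protocol*

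**What the plan says.** Section 5.1 (Predictors) sets the scope: "The current study will examine all 17 predictors included in the OxMIS tool". It then points to the definitions: "A list of the variables that will be employed in this analysis is presented below (see appendix A". Appendix A opens by saying what the table is: "The table refers to the variables as defined in the original Swedish cohort".

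In that table, row 5 is previous alcohol use, with the note "Previous diagnosis of alcohol use disorder". Row 6 is "Previous self-harm", a binary variable, with exactly the same note. Row 6 is complete (number, label, type, note), so this does not look like a table broken in conversion from PDF. No other section defines self-harm.

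Step (i) of the analysis (section 5.1, Strategy for analysis) means "applying the existing model directly, without adjusting model coefficients and without adjusting the estimate of baseline risk". Steps (ii) to (iv) follow only if performance is insufficient. They update the baseline risk, then add a single rescaling of the coefficients, then re-estimate a subset of coefficients as a last resort.

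Row 13 is labelled "Length of first inpatient stay > 7", with no unit. Its note reads "Hospitalized for at least one week during their first inpatient stay".

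**The concern.** A simple validation tests the published model only if each coefficient is multiplied by the variable on which it was estimated. Row 6 breaks that link for one of 17 predictors, and the protocol offers no correct text to fall back on. An analyst who sees the slip must find the definition elsewhere. One who does not see it will build the alcohol variable twice.

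Two things would be at stake. First, the performance reported for step (i) would not be that of OxMIS. Second, because insufficient performance in step (i) opens the updating sequence, a coding fault could be read as poor transport of the model to Finland, and the model could be revised for that reason. Neither a new intercept nor a single rescaling factor would put the self-harm weight back on the right people.

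**Working it through.** **The plan's own figure.** Section 5.2 expects 137,000 × 0.008 = 1096 suicides, 10.96 times the minimum of 100. This reproduces and does not depend on the point made here.

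**1. Rows 5 and 6 side by side.** The labels differ and the notes are identical. Literally, x6 = x5 for every patient, which leaves 16 distinct predictors against the 17 promised.

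**2. Step (i).** Write b5 and b6 for the existing alcohol and self-harm coefficients. The contributions to the linear predictor are:

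| Alcohol diagnosis | Self-harm | Intended | As written |
|---|---|---|---|
| no | no | 0 | 0 |
| yes | no | b5 | b5 + b6 |
| no | yes | b6 | 0 |
| yes | yes | b5 + b6 | b5 + b6 |

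The two middle groups are mis-scored.

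**3. How many patients.** The document gives no prevalences, so these are assumptions: self-harm prevalence s and alcohol prevalence a of 10%, 20% or 30% each, and an odds ratio between them of 1, 3 or 5. With p the share who have both, the wrongly coded share is s + a − 2p, and the share of true self-harm coded positive is p/s.

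- Smallest wrong share: s = a = 10%, odds ratio 5, p = 0.0297. 0.10 + 0.10 − 0.0594 = 0.141.
- Largest wrong share: s = a = 30%, odds ratio 1, p = 0.09. 0.30 + 0.30 − 0.18 = 0.42.
- Over the whole grid, 10% to 64% of true self-harm cases are coded positive.

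In 137,000 patients, 0.141 × 137,000 ≈ 19,300 and 0.42 × 137,000 ≈ 57,500 would carry the wrong value.

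**4. Calibration.** Assumptions: rare outcome (so odds ratios act as risk ratios), independent predictors, alcohol odds ratio 1.5, self-harm odds ratio R, and a model otherwise correct in Finland. Then

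- overall O/E = (1 − s + sR)(1 − a + 1.5a) / (1 − a + 1.5aR)
- O/E among true self-harm = R(1 − a + 1.5a) / (1 − a + 1.5aR)

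Example with s = 20%, a = 15%, R = 2: overall 1.20 × 1.075 / 1.30 = 0.99; among self-harm 2 × 1.075 / 1.30 = 1.65.

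| s / a | Overall O/E (R = 1.5, 2, 3) | O/E in self-harm (R = 1.5, 2, 3) |
|---|---|---|
| 20% / 15% | 1.00, 0.99, 0.99 | 1.36, 1.65, 2.11 |
| 10% / 30% | 0.88, 0.79, 0.67 | 1.25, 1.44, 1.68 |
| 30% / 10% | 1.07, 1.14, 1.24 | 1.40, 1.75, 2.33 |

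Risk in people with self-harm is under-predicted throughout. Overall O/E ranges from unremarkable to clearly wrong in either direction.

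**5. Discrimination.** The score loses the self-harm information and gives alcohol too much weight. No AUC figure is offered, because the loss depends on the spread of the other 15 predictors, which the document does not give.

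**6. Step (iv).** With x5 = x6, the data identify only the sum b5 + b6. A test matrix with an intercept, one other binary column and the alcohol column twice has rank 3 of 4. This matters only if both coefficients are in the re-estimated subset.

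**7. Row 13.** Read in days, the label codes a first stay of 7 days as 0 and the note codes it as 1. At 6, 8 and 9 days they agree.

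**The case against.** The best defence is that this is a visible copy-down slip that nobody would program. The row is still labelled self-harm. The table says that it describes the Swedish variables, so it reports definitions and does not set new Finnish ones. The protocol commits to 17 predictors, while the literal reading gives 16. Section 1 says that the development protocols and coefficients are published, and section 5.1 (Presentation of results) promises to report differences in variable definitions from the original cohort. Two identical rows in a descriptive table would also be hard to miss.

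Most of this stands, and it limits the consequence: mis-scoring depends on literal coding. It does not repair the text. The table is named as the list of variables for this analysis, and noticing that row 6 is wrong does not tell the analyst what is right.

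Three stronger readings are tempting and not supported:

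- A reader might infer that the study will be mis-scored. The label and the 17-predictor commitment point the other way, so the document supports only that it could be.
- A reader might infer that overall calibration would hide the error. That holds at 20%/15% in the table above and fails at the other two prevalence pairs.
- A reader might infer that re-estimation must break down. Step (iv) is a last resort on a subset of coefficients, and a dropped column would be more likely to expose the error than to conceal it.

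It is also fair to say that neighbouring rows give no diagnosis codes or look-back period. That detail may sit in an analysis plan not shown, and its absence is no part of this point.

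**Conclusion.** The point holds in conditional form. Row 6 is wrong as written, nothing else in the protocol corrects it, and section 5.1 makes the table operative. If it is followed literally, one of 17 coefficients is applied to the wrong patients, step (i) does not evaluate OxMIS, and updating could be triggered by a coding fault.

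The size is illustrative only. The 14–42% miscoded and the under-prediction among people with self-harm by a factor of about 1.25 to 2.3 rest on assumed prevalences and odds ratios. The second figure also assumes independent predictors and an alcohol odds ratio of 1.5. No direction can be claimed for overall O/E.

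The row 13 mismatch is real but minor. It concerns only first stays of exactly 7 days and should not be given the weight of row 6.

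**What to change.** Replace the note in row 6 with the self-harm definition used in the OxMIS development study. The detail given in neighbouring rows is enough, and codes can be left to the analysis plan. The documents do not show that definition, so it has to be taken from the development study's own records. Before scoring, cross-tabulate predictors 5 and 6 to confirm that they are different variables.

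In row 13, state one threshold with its unit in both label and note, taken from the development model.

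The cost is one table cell for the main point and one row for the side note. No new data are needed, and the expected 1096 events do not change. The correction should be made before the predictors are derived.
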